# Electro-acupuncture with different current intensities to treat functional constipation: a study protocol for a randomized controlled trial

**DOI:** 10.1186/1745-6215-14-344

**Published:** 2013-10-22

**Keywords:** Acupuncture, Functional constipation, Study protocol

## Abstract

**Background:**

Functional constipation (FC) is highly prevalent in the general population of the world and has a substantial negative impact on the health-related quality of life of individuals. Many clinical trials have indicated that acupuncture is effective in the treatment of FC. However, the sample sizes of these previous studies were too small. Furthermore, there are no reports investigating the relationship between the stimulation parameter and the therapeutic effect. We therefore designed a multicenter randomized controlled trial to address these problems and hopefully provide a more conclusive answer to these questions.

**Methods:**

Participants will be included if they meet all of the following conditions: (1) diagnosed with functional constipation according to the Roman III standard; (2) aged between 18 and 65 years; (3) not taking any drugs that promote gastrointestinal movements at least during the 1 week prior to randomization; (3) willing to sign an informed consent form; (4) willing to return to the study site for their study visits. The participants will be randomly assigned to three groups in a 1:1:1 ratio: high current intensity group, low current intensity group, and mosapride citrate control group. The total study period is 9 weeks for each patient, 1 week for baseline, 4 weeks for treatment, and 4 weeks for follow-up. The primary outcome in this trial is the number of defecating events per week. The secondary outcomes will include the shape and properties of the stool, intensity of defecating difficulty, Patient Assessment of Constipation Quality of Life (PAC-QOL), MOS item Short Form health survey (SF-36), Self-Rating Anxiety Scale (SAS), and Self-Rating Depression Scale (SDS).

**Discussion:**

This study will provide significant evidence for the application of acupuncture in FC and will identify a suitable stimulation parameter for treatment.

**Trial registration:**

ClinicalTrials.gov ID: NCT01274793.

## Background

Functional gastrointestinal disorders (FGIDs) are very common diseases worldwide [1]. Functional constipation is a common type of FGIDs described by persistently difficult, infrequent, or incomplete defecation that does not meet the IBS criteria [2]. Surveys have shown that the prevalence of functional constipation in the general population of the US and Asia is 12%-19% [3] and 14% [4], respectively.

The mean annual cost per patient with constipation is estimated to be $7,522 [5]. There are significant economic costs associated with treating functional constipation, including direct costs associated with evaluation and treatment, as well as indirect costs such as missing school or work or diminished productivity. Therefore, chronic constipation has a substantial negative impact on the health-related quality of life of individuals [6].

To treat chronic constipation, a number of lifestyle modification activities are recommended, such as consumption of a high fiber diet, frequent exercise, and drinking plenty of fluids. Conventional treatments for functional constipation include stool softeners, bulking agents, osmotic and stimulant laxatives, and lubiprostone (a chloride channel activator). However, a systematic review of chronic constipation conducted by the American College of Gastroenterology (ACG) Task Force showed that there is little evidence to support the use of many of these agents, with the exceptions of osmotic laxative lactulose and polyethylene glycol, which were found to improve stool frequency and stool consistency [7]. However, the sideeffects of laxatives cannot be ignored. Many patients have reported the effectiveness of laxatives, but their effects disappear when usage of the drugs stops.

Consequently, many constipation patients ask for additional help. Acupuncture, an important part of traditional Chinese medicine (TCM) that dates back at least 3000 years, can cure disease because it can stimulate the body’s self-regulatory ability, which is characterized by integrity and ambidirectional dominance. Acupuncture has gained increased popularity in Western countries because of its convenience, safety, and unique therapeutic effects. Both ancient literature and clinical practice have showed that acupuncture has many advantages for treating functional diseases of the nervous system, motor system, and digestive system, especially for functional bowel diseases, such as functional constipation, diarrhea, and dyspepsia. A number of clinical trials have shown that acupuncture is effective in the treatment of functional constipation, although the sample sizes of these trials were small. Furthermore, the effectiveness of acupuncture for the treatment of childhood constipation has been widely admitted [8-10]. However, as far as adult constipation is concerned, there are no randomized controlled trials (RCTs) that conclusively demonstrate the effectiveness of acupuncture. Furthermore, there are no reports of the relationship between the stimulation parameter and the therapeutic effect. We therefore designed a multicenter RCT to address these problems and hopefully provide a more conclusive answer to these questions.

The primary objective of this study is to investigate whether electro-acupuncture can effectively treat functional constipation through a comparison with mosapride citrate. The secondary objective is to determine whether different stimulation parameters (current intensities) result in different therapeutic effects for managing this condition.

## Methods

### Study design

A multicenter, randomized, parallel, controlled trial is currently being performed (Figure 1). Participants will be included from the following three hospitals: Affiliated Tongji Hospital of Huazhong University of Science and Technology, Affiliated Hospital of Hubei University of TCM, and Affiliated Hospital of Guangzhou University of TCM. Each research center must be in strict accordance with diagnostic standards, inclusion criteria and exclusion criteria.

**Figure 1 F1:**
[figure not shown]
Trial flow chart.

The research protocol has been approved by the Clinical Trial Ethics Committee of Tongji Medical College, Huazhong University of Science and Technology (approval no. FWA00007304) and registered on the ClinicalTrials.gov protocol registration system (https://register.clinicaltrials.gov, ClinicalTrials.gov ID: NCT01274793). Approval to conduct this study has also been obtained from the involved hospitals and corresponding ethics committees. Before randomization, all participants will be fully informed and provided enough time to decide whether they will take part in this trial. The participants will be asked to sign a written informed consent based on their own will. Patients will be recruited to join the study only once and will not receive any monetary compensation for their participation.

### Inclusion criteria

Participants will be included if they meet all of the following conditions: (1) diagnosed with functional constipation according to the Roman III standard; (2) aged between 18 and 65 years; (3) not taking any drugs that promote gastrointestinal movements at least during the 1 week prior to randomization; (3) willing to sign an informed consent form; (4) willing to return to the study site for their study visits.

### Exclusion criteria

Participants will be excluded if they meet any of the following conditions: (1) unconsciousness, psychosis or failure to express subjective symptoms (acupuncture is an invasive intervention that requires 30 min per treatment; therefore, to ensure safety, we will not include these patients); (2) pregnant women or women in their lactation period (because it is still unclear whether acupuncture will lead to abortion or other side effects); (3) complicated with serious diseases of the heart, liver, kidney, and other organs; (4) bleeding disorders (acupuncture is invasive, and the procedure involves penetration of the skin; therefore, patients with bleeding tendency will be excluded); (5) previous participation in this study.

Patients have a choice whether to participate in the study, and they may withdraw their consent at any time. Their consent or lack thereof will not affect their deserved treatments.

### Recruitment strategies

Four strategies will be used to recruit participants with functional constipation: hospital-based recruiting, university-based recruiting, community-based recruiting, and television and newspaper advertisements. Hospital-based recruiting will involve the recruitment of participants in outpatient departments from the three hospitals, mainly from the digestion and acupuncture departments. Posters of this trial will be shown outside of the departments or hospitals to attract possible candidates. As to university or community recruiting, leaflets will be sent out to universities or communities near the research centers, and posters will be posted in the campus or community to enhance awareness. In addition, advertisements through TV, broadcasts, newspapers, and so on will be used to attract more patients.

### Sample size

Sample size calculation is based on a study by Camilleri:A placebo-controlled trial of prucalopride for severe chronic constipation [J]. N Engl J Med, 2008, 358 (22): 2344–2354 [11]. After drug treatment, the average defecation rate of patients with functional constipation was 2.6 times per week, with a standard deviation of 2.2. Furthermore, there was a 1.4-fold difference in the clinical effects between the drug and the placebo. Therefore, based on this study along with our preliminary test, the mean defecating frequency is 4.0 after acupuncture treatment, with a standard deviation of 3. To detect this difference, we need a minimum total sample size of 213 [71 for each group (α = 0.05, β = 0.10)] [12]. To allow for a loss of 15%, a total sample size of 243 (81 for each group) is required.

### Randomization and blinding

The participants will be randomly assigned to three groups through complete randomization at a 1:1:1 ratio equally among the three centers: high current intensity group, low current intensity group, and mosapride citrate control group. Therefore, each group in each center will have 27 participants. The randomization sequence will be generated using R2.0 software. A designated researcher will prepare the assignments in opaque envelopes in sequence.

The acupuncturists will only know of the grouping scheme just prior to the treatment to ensure that the trial will be as blinded as possible. The researchers will not be permitted to predict a patient’s assignment or change it after the patients are randomized. Blinded evaluation (the curative effect will be evaluated by a third party who does not know the grouping) and blinded statistical analysis will be emphasized during the data collection and analysis stage.

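### The named method, complete randomization, does not guarantee the stated 27 patients per arm in each centre, so the method or the count must be corrected to match the list in use

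*Protocol article*

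**What the plan says.** The Randomization and blinding section of the protocol article gives the method and the allocation together: "The participants will be randomly assigned to three groups through complete randomization at a 1:1:1 ratio equally among the three centers". The three groups are high current intensity, low current intensity and mosapride. The next sentence draws a consequence: "Therefore, each group in each center will have 27 participants".

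On how the list is made and delivered, the section adds only "The randomization sequence will be generated using R2.0 software" and "A designated researcher will prepare the assignments in opaque envelopes in sequence". It does not define complete randomization, and it mentions no blocks, fixed totals or stratification by centre.

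The figures behind the 27 are in two other sections. Sample size says that "a total sample size of 243 (81 for each group) is required", and Study design names three hospitals.

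**The concern.** Complete randomization is commonly used as a synonym for simple, unrestricted randomization. Under that method an arm's count in a centre is a random quantity, and no count follows from the method with certainty. The article nevertheless presents 27 per cell as a consequence of it. An exact 27 requires a restriction within each centre, such as a fixed list of 81 with 27 of each treatment or blocks that add up to the same totals, and it also requires each centre to enrol exactly 81.

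Two things depend on which method is real:

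- **Predictability.** Needling and tablets are visibly different. With a fixed, known total per arm and centre, staff who keep a count can infer late assignments, and the last one is fully determined. An unrestricted list carries no such risk. The same section says that researchers may not predict assignments.
- **Analysis.** If allocation was balanced within centre, centre is a design factor. A comparison that ignores it gives standard errors that are too large when centres differ. The Statistical analysis section names a between-group analysis of variance and does not mention centre.

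**Working it through.** **Inputs from the protocol article**

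- Total 243, 81 per arm (Sample size)
- 3 centres (Study design)
- 3 arms, 1:1:1, divided equally among centres (Randomization and blinding)

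**Step 1. The plan's own figure.** 243 / (3 arms × 3 centres) = 27. The arithmetic is right, and 27 is the expected cell size.

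**Step 2. Chance of exactly 27/27/27 under unrestricted assignment.** Assume 81 patients in a centre, each assigned independently with probability 1/3 per arm.

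- One centre: 81! / ((27!)³ × 3⁸¹) = 0.0101, about 1%.
- All three centres: 0.0101³ = 1.04 × 10⁻⁶, about 1 in a million.

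**Step 3. Spread of one arm's count in one centre.**

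- SD = √(81 × 1/3 × 2/3) = √18 = 4.24.
- 95% range: 27 ± 1.96 × 4.24 = 18.7 to 35.3, about 19 to 35.
- In a simulation of 200,000 trials, the median gap between the largest and smallest arm in a centre was 8 (5th to 95th percentile 2 to 17).

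**Step 4. The same count under a fixed list.** If each centre has a list of 81 with 27 of each arm in random order, and enrols exactly 81, the chance of 27/27/27 is 1.

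**Step 5. What the chance imbalance costs.**

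- Overall arm size has variance 243 × 2/9 = 54. The variance of a between-arm difference is proportional to 1/n, which rises on average by about 54 / 81² = 54 / 6561 = 0.8%. That equals 0.008 × 81, or about 0.7 of a patient per arm.
- Taking each arm-by-centre cell separately is harsher: 18 / 27² = 18 / 729 = 2.5%, or about 2 patients per arm.
- To turn this into power, assume a two-sided 5% comparison of two means, a difference of 4.0 − 2.6 = 1.4 and a pooled SD of √((2.2² + 3²)/2) = 2.63. Power is then 88.7% with 71 per arm and 92.3% with 81. That is 3.6 points over 10 patients, or about 0.36 points per patient. The loss is about 0.7 × 0.36 = 0.25 points by the first figure and 2 × 0.36 = 0.7 points by the second.

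Both are under one percentage point.

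**The case against.** The strongest reply is that the article never defines complete randomization and never says that patients are assigned independently. Its wording, "complete randomization at a 1:1:1 ratio equally among the three centers", followed by the count of 27 and by envelopes prepared in sequence, fits a fixed list of 81 per centre under a loose label. On that reading 27 is right and only the name of the method is imprecise. The probabilities in steps 2 and 3 then do not apply. This reading is plausible and cannot be excluded. It does not remove the need for a correction, because the label would then describe a method that was not used.

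A reader might infer more than the document supports:

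- **That 27 per cell is impossible under the named method.** It is very improbable, not impossible. The method does not guarantee it.
- **That unequal cells would confound treatment with centre or cost serious power.** Under unrestricted assignment, treatment is independent of centre. Any imbalance is due to chance, is not systematic bias, and costs little (step 5).
- **That the scheme should be replaced for the remaining patients straight away.** If a 27/27/27 list per centre is in use, dropping it midway would lose the planned balance. Short permuted blocks may also be more predictable than one list of 81 when treatment is visible to the acupuncturist.

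A further reply is that block details and model terms usually belong in the full protocol or analysis plan, which is not shown. That is accepted: their absence from the article is not the point. The point is that a stated method and a stated consequence do not fit together. Centre enters the analysis only if the list turns out to have been balanced within centre.

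**Conclusion.** The point holds as an inconsistency between the named method and the stated allocation. If complete randomization means unrestricted assignment, and each centre enrols 81, then 27 per arm in every centre is an expectation with about a 1% chance of being met exactly in one centre and about 1 in a million in all three. No other section reconciles the two statements.

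The document does not show which of the two is wrong. Either the list is unrestricted and the count is overstated, or the list is restricted within centre and the method is misnamed. The consequence for power is small in either case. The consequence for reporting, for judging predictability and for choosing the analysis is what justifies a correction.

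**What to change.** First verify which list has been used since the first patient. The Trial status section reports 123 patients recruited by 15 March 2013, leaving 243 − 123 = 120 of the target at that date. Then amend the Randomization and blinding paragraph to match:

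- **If the list is restricted within centre** (fixed totals or blocks): replace the term complete randomization with the centre-stratified method actually used. Say that 27 per arm holds only if each centre enrols 81. Include centre as a factor in the primary comparison.
- **If the list is unrestricted:** keep the method and give 27 as an expected number per arm and centre. Centre-stratified allocation with concealed, varying block sizes for the remaining patients is then an option, not a requirement. If it is adopted, the change of method and its date should be reported.

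The cost is one check of the list and one amended paragraph, plus one extra model term in the restricted case. It needs no new patients or visits. The optional change of scheme would cost more, because it alters allocation partway through recruitment.

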### Interventions

The total study period will be 9 weeks for each patient, 1 week for baseline, 4 weeks for treatment, and 4 weeks for follow-up (5 to 8 weeks after randomization at 0 week) (Figure 2). Participants in the electro-acupuncture groups will receive 16 acupuncture treatments: five times per week (once a day for 5 days continuously, followed by a 2-day interval) during the first 2 weeks and three times per week (once every 2–3 days) during the following 2 weeks. Each session will last 30 min.

**Figure 2 F2:**
[figure not shown]
The total study period and the timepoint of evaluation.

Acupoints Quchi (LI11) and Shangjuxu (S37) will be used on both sides, which is consistent with the principles of traditional acupuncture theories. Sterile, disposable needles made in Shanghai, China, will be used in this trial. The needles will be 25 to 50 mm in length and 0.3 mm in diameter. De qi sensation will be achieved in the acupuncture groups through lifting and thrusting movements combined with twirling and rotating the needles. After being acupunctured, the points will be punctured again using auxiliary needles 2 mm lateral to the first needle, to a depth of 2 mm, without manual stimulation. The auxiliary needles will be of the same brand, being 13 mm in length and 0.18 mm in diameter. The acupuncture needle and auxiliary needle of each point will be connected to form a circuit containing a HANS-200E stimulator (Nanjing Jisheng Co., China) for 30 min. The reason behind using the auxiliary needle is to guarantee the current confined in each acupoint. The stimulation parameters of electro-acupuncture in the high current intensity group will be an alternating wave with a frequency of 2/50 Hz; the current will be strong enough to reach the patients’ tolerance threshold value (1.0-1.8 mA, based on preliminary results). The frequency will be the same in the low current intensity group; while the current (0.2-0.7 mA) applied to this group will be relatively weak, it will be clearly perceived by the participants.

Participants in the control group will be orally administered 5 mg mosapride citrate tablets three times a day for 4 continuous weeks.

### Outcome measures

All of the participants in this trial will be asked to update constipation diaries from 1 week before randomization to 8 weeks after randomization. Only when they are eligible in the baseline phase for this study will the participants be asked to make diary entries from 0 to 8 weeks after randomization.

The primary outcome in this trial is the number of defecating events per week at baseline and at the 2nd, 4th and 8th week after randomization (Table 1 and Figure 2). Secondary outcomes include the following five aspects: shape and properties of stool, intensity of defecating difficulty, Patient Assessment of Constipation Quality of Life (PAC-QOL), MOS item Short Form health survey (SF-36), Self-Rating Anxiety Scale (SAS), and Self-rating Depression Scale (SDS). The first three of the secondary outcomes will be measured at baseline and at the 2nd, 4th and 8th week after randomization. The other secondary outcomes will be measured at baseline and at the 2nd and 4th week after randomization, although SF-36 will be measured only before randomization and 4 weeks after randomization. Additionally, the time of the first spontaneous defecation (from the end of the first intervention to the first spontaneous defecation) will be recorded.

**Table 1 T1:** Trial process

	**Baseline**	**Treatment**			**Follow-up**
**Time**	−1w	0w	2w	4w	8w
**Assessment**		1st	2nd	3rd	4th

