**Outcomes**					
Number of defecating events per week		√	√	√	√
Shape and properties of stool		√	√	√	√
Intensity of defecating difficulty		√	√	√	√
PAC-QOL		√	√	√	√
SF-36		√		√	
SAS		√	√	√	
SDS		√	√	√	
The time of the first spontaneous defecation					

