### Statistical analysis

Statistical analyses will be undertaken by the Department of Epidemiology and Biostatistics, School of Public Health, Tongji Medical College, Huazhong University of Science and Technology. Baseline characteristics of the subjects will be described by descriptive analysis and analyzed by analysis of variance, *χ*^2^-test, and others. With regard to the effects of intervention, the *χ*^2^-test will be applied to compare frequencies between groups, such as the number of defecating times per week; analysis of variance will be performed for comparison of continuous parameters between the groups (α = 0.05). All of the analyses will be based on both an intention-to-treat analysis (ITT) and a treated-per-protocol analysis (TPP).

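### The primary outcome lists weeks 2, 4 and 8 (with baseline) but does not say which post-baseline week, or which summary over weeks, is the primary result

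*Protocol article*

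**What the plan says.** - **Outcome measures:** "The primary outcome in this trial is the number of defecating events per week at baseline and at the 2nd, 4th and 8th week". No visit is singled out, and no change from baseline, average over weeks or success rule is given.
- **Abstract, Methods:** "The primary outcome in this trial is the number of defecating events per week", with no time point.
- **Table 1, Outcomes:** the row "Number of defecating events per week" is ticked at weeks 0, 2, 4 and 8 alike.
- **Interventions:** the schedule is "1 week for baseline, 4 weeks for treatment, and 4 weeks for follow-up". Weeks 2 and 4 are therefore on treatment, and week 8 is four weeks after treatment ends.
- **Sample size:** one pair of means, 2.6 per week (SD 2.2) and 4.0 per week following acupuncture (SD 3), with alpha 0.05 and beta 0.10, gives 71 per group. The week is not named.
- **Statistical analysis:** for this outcome a chi-square "test will be applied to compare frequencies between groups, such as the number of defecating times per week"; separately, "analysis of variance will be performed for comparison of continuous parameters between the groups". The only level given is 0.05, with no ordering of visits and no adjustment over them.

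**The concern.** A primary outcome has to reduce to one result, or come with a rule for combining several. Here the definition is a list of visits. Baseline precedes treatment and cannot show an effect, which leaves three candidates: response halfway through treatment, response at its end, and persistence four weeks later.

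These can diverge, and the article gives a reason to expect it: the Background notes that the benefit of laxatives is lost once they are stopped. If an electro-acupuncture arm beat mosapride at week 4 but not at week 8, or at week 2 only, the article does not say whether the primary objective was met. The choice could then be made after the results are known.

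**Working it through.** **1. Reproduce the planned sample size.** Inputs from the Sample size section: difference 4.0 − 2.6 = 1.4; SDs 2.2 and 3; alpha 0.05; power 0.90. Two-sided testing is assumed because the article does not state sidedness.

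n per group = 2 (z₀.₉₇₅ + z₀.₉₀)² SD² / 1.4², with (1.960 + 1.282)² ≈ 10.51.

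- SD = (2.2 + 3)/2 = 2.6: n = 2 × 10.51 × 6.76 / 1.96 ≈ 72.5, so 73.
- SD = √((2.2² + 3²)/2) = √6.92 ≈ 2.63: n = 2 × 10.51 × 6.92 / 1.96 ≈ 74.2, so 75. With 71 per group the power is 0.887.

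The stated 71 is thus approximately reproduced as a single two-sided comparison, at one unnamed time, using the full 0.05.

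**2. What if all three weeks counted, with a Bonferroni split?** Alpha = 0.05/3, z ≈ 2.394, and (2.394 + 1.282)² ≈ 13.51.

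- SD 2.6: 2 × 13.51 × 6.76 / 1.96 ≈ 93.2, so 94 per group.
- SD 2.63: 2 × 13.51 × 6.92 / 1.96 ≈ 95.4, so 96 per group.
- Power at each week at that level (SD 2.63): 0.78 with 71 per group, 0.84 with 81.

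The planned size therefore suits one primary result, not three with alpha divided among them.

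**3. What if any one week were enough, each tested at 0.05?** This rule is assumed for illustration; the article does not state it. For independent weeks, 1 − 0.95³ = 14.3%. Repeated counts on the same patients are correlated, and the article gives no correlation, so a range is shown. One million draws of three equally correlated normal test statistics, with success if any exceeds 1.96 in absolute value, give:

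| Assumed between-week correlation | Type I error, one pairwise contrast |
|---|---|
| 0.3 | 13.6% |
| 0.5 | 12.5% |
| 0.7 | 10.9% |
| 0.9 | 8.4% |

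The range is about 8% to 14%, against a nominal 5%.

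**The case against.** The strongest reply is that this is a condensed article and the analysis plan is not shown. A visit-by-visit strategy, a model over visits or a multiplicity rule may sit there. That stands: the absence of alpha control is not the point made here. The primary time point is different, because it belongs to the outcome definition, and the article does give that definition.

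Several stronger readings are tempting but not supported:

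- **Four chances to succeed, each tested at 0.05.** The Statistical analysis section does not say that each visit is tested separately. Baseline is most naturally a reference measurement: the sentences that follow use the same wording as a measurement schedule for the secondary outcomes. At most three visits could show an effect.
- **An error rate of 19% to 24%.** This is the any-week figure when both electro-acupuncture arms are compared with mosapride (correlation 0.7 to 0.3). Two such contrasts already give about 9% at a single week. That part comes from the number of arms and would remain after a week is named.
- **Error rates for a three-group analysis of variance.** The article assigns that test to continuous parameters and names the chi-square test for weekly defecations, so those rates do not describe the stated plan for this outcome.
- **The sample size already fixes week 4.** It speaks only of the frequency after acupuncture treatment. End of treatment is the natural reading, but no week is given, and the same difference could have been assumed at every visit.

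**Conclusion.** The point holds in this form: the primary outcome is a list of visits, and nothing in the article designates one post-baseline week or one summary over weeks as primary. This rests on the text alone and needs no assumption. Its main consequence is that the primary result is undefined if the weeks disagree.

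The error-rate consequence is conditional. If success at any one week were claimed from separate unadjusted tests, the type I error for one pairwise contrast would be about 8% to 14% instead of 5%, for between-week correlation of 0.9 down to 0.3. Both the any-week rule and the correlations are assumptions. The article does not show that the trial will be analysed this way, only that its definition leaves room for it.

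**What to change.** Before unblinding, name one primary endpoint: weekly defecations at week 4 (end of treatment), compared between groups with adjustment for the baseline count already collected. Week 4 is the choice most consistent with the sample-size text, though not one that the text fixes. A prespecified summary over weeks would also remove the ambiguity. Make weeks 2 and 8 secondary, for onset and durability.

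**Cost.** A result at week 2 or week 8 alone can no longer be claimed as primary. The chi-square test now named for this outcome must be replaced by a baseline-adjusted model, so the Statistical analysis section changes as well as the outcome definition. No extra patients are needed, since the planned size already corresponds to one comparison at full alpha. The Trial status section reports 123 recruited by 15 March 2013, against a target of 243, with recruitment continuing. On that status the change could still be made before unblinding.

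### Time to first spontaneous defecation starts at the end of the first intervention, which is defined for an acupuncture session but not for the mosapride tablets

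*Protocol article*

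**What the plan says.** After the primary and secondary outcomes, Outcome measures adds one more item, introduced by "Additionally, the time of the first spontaneous defecation". The clock runs "from the end of the first intervention to the first spontaneous defecation", with the same wording for all three arms. Table 1 gives the measure a row under Outcomes ("The time of the first spontaneous defecation").

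Interventions describes two different kinds of treatment. The acupuncture arms have 16 separate sessions: "Each session will last 30 min". The control arm takes "5 mg mosapride citrate tablets three times a day for 4 continuous weeks".

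Statistical analysis gives general rules by type of variable. For counts, a chi-square "test will be applied to compare frequencies between groups, such as the number of defecating times per week". For the rest, "analysis of variance will be performed for comparison of continuous parameters between the groups". It names no time-to-event method and assigns no method to this measure by name. Diaries run to 8 weeks after randomisation.

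**The concern.** A time to event can be compared between arms only if the clock starts at the same kind of moment in each. Here the start is the end of a session, and the tablet arm has no session. The first intervention in that arm could end with the first tablet, with the last tablet of day 1 or, less plausibly, with the course. Sites may record it differently, and an analysis plan cannot later recover a time zero that was not recorded consistently. Because the ambiguity exists in one arm only, randomisation does not balance it. It falls on the contrast with mosapride, which is the primary objective, although on a minor measure.

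The second part is the method. A duration would come under the general analysis-of-variance rule by default. That rule has no way to use a participant who withdraws before a first stool, and waiting times are usually skewed.

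**Working it through.** The article states no figure for this measure, so there is none to reproduce. The planning values in Sample size give the scale: 2.6 stools per week (SD 2.2) after drug treatment and 4.0 (SD 3) after acupuncture. I assume these rates apply from the first treatment and that all these stools count as spontaneous.

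**1. The time origin**

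- Mean wait, one constant rate for all patients: 168/2.6 = 64.6 h and 168/4.0 = 42.0 h.
- First versus last tablet of day 1, 12 h apart (assumed): 12/64.6 = 19% of the control wait. If the gap were 24 h: 24/64.6 = 37%.
- End of a 30-minute session versus its start: 0.5/64.6 = 0.8% and 0.5/42 = 1.2%.
- Chance that a control has a stool inside the 12 h, exponential times: 1 − exp(−12/64.6) = 17%. Under the later start that stool would no longer count.

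If rates vary between patients (gamma, step 2), the mean wait is longer: 64.6 × 3.02/(3.02 − 1) = 97 h. The 12 h is then 12/97 = 12% of it.

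These ratios show how far the two readings differ for the same stool. They do not estimate bias in the arm mean. With a constant rate, the mean wait to the next stool is the same from either start, because stools before the clock are passed over. With more regular stools, or an effect that begins at the first dose, the mean would move.

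**2. How many would have no event**

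With a negative binomial matched to each mean and SD, k = mean²/(SD² − mean). This gives 2.6²/(2.2² − 2.6) = 3.02 and 4.0²/(3² − 4.0) = 3.20. The share with no stool by week w is (k/(k + mean × w))^k.

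| Week | 2.6 per week | 4.0 per week |
|---|---|---|
| 1 | 15.3% | 7.5% |
| 2 | 4.9% | 1.8% |
| 4 | 1.1% | 0.3% |
| 8 | 0.2% | 0.05% |

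Over the 8-week diary the expected number is 81 × 0.00196 + 162 × 0.00047 = 0.16 + 0.08 = 0.2 of 243. If spontaneous stools were much rarer, at an assumed Poisson 0.5 per week, exp(−0.5 × 8) = 1.8% would have none. At 0.25 per week it would be exp(−0.25 × 8) = 13.5%.

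**3. What the method change gains**

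Simulated two-arm comparison: 81 per arm, 2.6 versus 4.0 per week, 8 weeks of observation, two-sided 5%.

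- Exponential times, one rate per arm: about 78% power for both analysis of variance and log-rank.
- Rates varying between patients as the stated SDs imply: about 50% for analysis of variance and about 58% for log-rank. Almost everyone still has an event, so the difference comes from the long right tail.

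**The case against.** The best defence of the clock is that the first intervention naturally means the first treatment given. Swallowing a tablet takes a moment, so its end is its intake, and the arms then differ only by the 30-minute session, about 1% of the wait. That reading is reasonable and may be what was meant. The article does not state it, however, and dosing three times a day leaves another reading open.

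On the method, analysis of variance is a general rule, this is a condensed article, and an analysis plan that is not shown may treat this measure differently. That stands: the article does not fix a wrong method for this measure by name. It is still the only rule given that would cover a duration.

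A reader might infer that analysis of variance would discard many poor responders, bias the result towards no difference and lose much power. That would need observation to close after about a week. The diary runs 8 weeks, and at the planning rates almost nobody then lacks an event. The 15% allowance for loss matters only for those who leave before their first stool, which is typically expected within days.

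A reader might also infer that the arms in general are not compared fairly. The documents do not support that. Both acupuncture arms share one time origin, the primary and listed secondary outcomes do not use this clock, and no sample size or stated hypothesis rests on the measure.

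**Conclusion.** The point holds in a narrow form, at low severity. The tablet arm has no stated counterpart to the end of a first session, so acupuncture versus mosapride on time to first spontaneous defecation lacks a common time zero. The two plausible day-1 readings differ by about 12 h. That is 19% of the mean control wait if every patient has the same rate, and about 12% if rates vary as the SDs imply. The 12 h spacing and the use of the planning rates from the first treatment are assumptions.

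The case for a time-to-event method is weaker. The gain is about 8 percentage points of power if rates vary between patients, and none with exponential times. There is also a small benefit from using the few early withdrawals properly.

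**What to change.** Define the start of the clock once, in words that apply to every arm: the start of the first treatment (first session or first tablet), or randomisation. State that the arms will be compared by Kaplan-Meier curves with a log-rank test or Cox model, and that participants with no spontaneous stool are censored at their last diary entry. State also that this replaces the general analysis-of-variance rule for this measure.

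The change is a few sentences in the protocol and analysis plan. It needs the date and time of the chosen start on file in all arms; the first stool is already to be recorded. Trial status reports 123 participants recruited by 15 March 2013, which is 123/243 = 51% of the target. For those already enrolled, start times may have to be retrieved, and any that cannot be found should be reported.
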